## **LIST OF ABBREVIATIONS**

| Abbreviation | Definition                                |
|---------------------|--------------------------------------------------|
| AE                  | Adverse event                                    |
| AF                  | Atrial fibrillation                              |
| CABG                | Coronary artery bypass grafting                  |
| CCS                 | Canadian Cardiovascular Society                  |
| CCTA                | Cardiac computer tomography angiography          |
| CK-MB               | Creatine kinase myocardial b fraction            |
| CPB                 | Cardiopulmonary bypass                           |
| CRF                 | Case report form                                 |
| CV                  | Cardiovascular                                   |
| DHA                 | Docosahexaenoic acid                             |
| DSMB                | Data safety monitoring board                     |
| ECG                 | Electrocardiogram                                |
| eGFR                | Estimated Glomerular Filtration Rate             |
| EHA                 | Eicosapentaenoic acid                            |
| GCP                 | Good Clinical Practice                           |
| ICU                 | Intensive care unit                              |
| IRB                 | Institutional Review Board                       |
| IVRS                | Interactive voice activated randomization system |
| LA                  | Left atrium                                      |
| LITA                | Left internal thoracic artery                    |
| LV                  | Left ventricle                                   |
| LVEF                | Left ventricular ejection fraction               |
| MACE                | Major adverse cardiac event                      |
| MI                  | Myocardial infarction                            |
| NSAIDS              | Non-steroidal anti-inflammatory drugs            |
| OAC                 | Oral anticoagulant                               |
| PCI                 | Percutaneous coronary intervention               |
| PHRI                | Population Health Research Institute             |
| RA                  | Radial artery                                    |
| RBC                 | Red blood cells                                  |
| RCT                 | Randomized controlled trial                      |
| REB                 | Research Ethics Board                            |
| RR                  | Relative risk                                    |
| SAE                 | Serious adverse event                            |
| SV                  | Saphenous vein                                   |
| SVG                 | Saphenous vein graft                             |

## **1 INTRODUCTION AND RATIONALE**

### **A. INTRODUCTION**

The SUPERIOR SVG trial is a prospective, international, multi-centre randomized controlled clinical trial (RCT). It utilizes a factorial design to elucidate the benefits of two interventions, one surgical and the other pharmacological. Both impact an important, contemporary clinical problem – poor saphenous vein graft (SVG) patency after coronary artery bypass grafting surgery (CABG).

#### **I. The problem to be addressed**

According to serial angiographic observational studies and pivotal trials on the benefit of antiplatelet medications on SVG patency, 1-year SVG occlusion rates are estimated to be 10-15% (1-4). Contemporary studies demonstrate SVG failure remains a significant issue of even greater importance than in previous decades. The PREVENT IV multi-centre trial (JAMA, 2005) enrolled 3,014 CABG patients - one of the largest CABG trials ever, *the* largest CABG trial with angiographic follow-up (5). The authors found at 1 year: 45% of ***all patients*** had >1 SVG occluded; 25% of ***all SVGs*** were occluded. Recent single centre trial data from Sunnybrook evaluating the role of intraoperative Graft Imaging to Improve Patency (GRIIP) also demonstrated that 30% of all patients have ≥1 SVG occluded by ~1 year (6). In contrast, the multi-centre Radial Artery Patency Trial (RAPS), compared the patency of the RA to SVG in patients who served as their own controls (7). The results showed 8% of radial artery bypass conduits and 13% of SVG conduits, were occluded at 1-year angiography – however these occlusions were in study vein grafts, implying a much higher rate of occlusion if the non-study grafts had been included. Perhaps more importantly, RAPS patients were largely recruited from the 1990's whereas PREVENT IV and GRIIP patients were enrolled since 2000. Furthermore, the importance of graft patency is highlighted from the results of PREVENT IV; patients with at least one SVG occluded had two times the incidence of perioperative myocardial infarction (MI), and thirteen times the composite endpoint of death, late MI or repeat revascularization at 12-18 months, compared to patients who had completely patent grafts (5).

#### **II. The need for this trial**

Early and late success of CABG is the result of sustained patency of the bypass grafts. Graft failure due to intimal hyperplasia and the progression of atherosclerosis is a complex, multifactorial inflammation process. It is initiated largely in areas of endothelial injury, secondary to biomechanical disturbances or trauma, or systemic factors such as lipoprotein disturbances and endothelial dysfunction. Accumulating data indicate that structural and/or functional alterations in endothelial integrity play a primordial role in the development of atherosclerosis via promoting aberrant interactions between modified lipoproteins, macrophages and other cellular elements of the vascular wall, inciting early plaque formation. As such, ***strategies, either pharmacological or mechanical in nature, which reduce and/or restore endothelial homeostasis remain an important cornerstone to limit atherosclerosis and vascular graft failure.***

While definitely more invasive, historically CABG has been more effective and durable than percutaneous coronary intervention (PCI) for the treatment of left main and multivessel coronary artery disease (8-10). However, the results (7-17), indications (16-17) and volume of PCI have expanded significantly, such that patients referred for CABG have more challenging coronary

anatomy, with diffuse, severe, small vessel (<2 mm), calcific disease. It is this recent change in the target vessels in contemporary CABG patients, which most likely explains the apparent decrease in 1-year SVG patency over the last decade (18).

This study aims to favourably impact SVG patency by integrating surgical and pharmacological approaches which address both the mechanical and biochemical pathways contributing to accelerated atherosclerosis, subsequent graft failure and poor clinical outcomes; we have designed a factorial 2x2 randomized controlled clinical trial to efficiently test both interventions.

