|                                        | 
patients with <math>\geq 1</math> graft with a significant (50-99%) stenosis at 1-year post-CABG angiography, compared to those who received placebo.
 
ii. The incidence of the composite of non-fatal MI (using new definition), all-cause mortality, and repeat revascularization (redo CABG or PCI) perioperatively and at 1 year is lower in the fish oil versus placebo group of patients.
 
Tertiary Outcome
 
Surgical Arm: The two groups will be compared with respect to the incidence of the composite endpoint of perioperative and 1-year non-fatal MI (using old definition), all-cause mortality, repeat revascularization (redo CABG or PCI) (major adverse cardiac events, MACE) and stroke.
 
Pharmacological Arm: The two groups will be compared with respect to the incidence of the composite endpoint of perioperative and 1-year non-fatal and fatal MI (using old definition), death, repeat revascularization (redo CABG or PCI) (major adverse cardiac events, MACE) and stroke.
 |
| Statistical Considerations             | 
Intention to treat analysis
 
Comparison of the proportion of patients developing the primary outcome at 1-year using Pearson chi-square test.
 
Overall type 1 error rate at 5%
                                                                                                                                                                                                                                                                                                                                                                                                                                                                                                                                                                                                                                                                                                                                                                                                                                                                   |

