All patients will have their left anterior descending coronary artery grafted with an internal thoracic artery, the standard of care for CABG. The study SVG, directed to the most important target intended for a venous conduit, may be to the second, third or fourth territory chosen; this design allows for the use of multiple arterial grafting as per surgeon discretion/patient indication. The surgeon will identify the proposed target for the study graft prior to surgery. While the site of SVG harvesting (right or left leg) and the coronary target grafted (circumflex, right coronary, or branch [i.e. diagonal]) will not be randomized, all site and target vessel characteristics will be recorded for post-hoc multivariable regression analysis. Surgeons will be encouraged to use the study SVG for a single distal target. If a sequential graft is required, it will only be considered patent at follow-up angiography if it is entirely patent to all sequentially grafted targets. If more than one SVG is used, surgeons will also be encouraged to harvest all SVGs using the same technique (either all “no touch” or all conventional). While this decision will not impact the primary outcome of ‘study graft’ patency between the two groups (i.e. the SVG directed to the most important vein graft target), it may increase the ability to detect differences in clinical outcomes at 1-year.

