### **8.2 Analysis population**

The main analysis will be by an intention-to-treat approach (i.e., all randomized patients in the study will be included in the analysis). At least 1,550 patients will be equally allocated to the four treatment groups.

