### **8.3 Statistical Methods**

The primary comparison for the 2 main study questions (“no touch” vs. conventional SVG harvesting [primary endpoint: study SVG occlusion]; fish oil supplementation vs. placebo [primary endpoint: proportion of patients with >1 graft occluded]) will be performed using a Chi-square test according to the intention-to-treat principle. A test for interaction will be tested similarly and with logistic regression. Statistical significance is assumed for  $p < 0.05$ . The secondary graft occlusion endpoints, graft stenosis, or graft occlusion or significant stenosis, will also be tested with Chi-square or Fisher’s tests where appropriate, considering graft stenosis as a dichotomous variable, as well as logistic regression treating graft stenosis as an ordinal variable. Additional modeling will be performed post hoc with logistic regression, generalized estimating equation and bootstrapping techniques, to evaluate covariates of graft occlusion (7,18,71). Variables of interest in addition to the usual demographic factors include: open vs. endoscopic vein harvesting, serum lipid values; study centre; surgeon; time period of patient entry (to address a possible learning effect); timing of postoperative angiography; parameters related to the distal coronary artery target such as, size, quality, and factors related to the specific coronary artery grafted including the severity of the proximal stenosis. Other categorical outcomes (major cardiac events and vein harvest site complications) will also be compared with either Chi-square or Fisher’s Exact test where appropriate. The harvest site infection scores will be tested using t tests.

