## 8.5 Sample size calculation

### A. SURGICAL ARM

The sample size estimation is based on the current prevalence of 1-year SVG occlusion using the conventional harvesting technique to be 20% (5,6). We consider a 30% relative risk reduction (RRR) in graft occlusion using the “no touch” technique to be a clinically important difference, consistent with RRRs reported for previous interventions to improve graft patency (antiplatelet therapy, use of statins post CABG, radial versus saphenous veins) and very conservative in terms of Souza’s clinical trial results (45,46). A sample size of 615 patients in each group will provide 80% power for a 2-tailed alpha of 0.05, to identify a RRR of 30% (20% occlusion rate in the control/ conventional harvesting group, to 14% in the experimental/”no touch” group – see Table 2a).

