### B. PHARMACOLOGICAL ARM

The literature suggests that fish-oils provide a RRR of about 25% compared to placebo (54,55, 65,69). Given a two-tailed alpha of 0.05, and an estimated 30% of control patients with  $\geq 1$  graft occluded at 1-year, a sample of 540 patients in each group (fish-oil versus placebo) will provide a power of 80% to detect a RRR of 25%. A sample size of 615 patients (required for the surgical intervention) provides approximately 85% power to test the fish oil hypothesis (see Table 2b).

We anticipate that 80% of patients will undergo 1-year coronary CT angiography, which is consistent with our past trial experience (7). The primary reason that patients failed to undergo late angiography in RAPS was late withdrawal of consent in 77 patients, protocol violation in 17 patients, new contraindication precluding research angiography in 19 patients and death in 8 patients (7). To adjust for this potential loss to follow-up angiography, the corrected sample size is 769 patients in each surgical group to ensure adequate statistical power when making our conclusions for both arms of the factorial design. Thus we aim to recruit a **total of 1,550** patients for the overall study across ~50 participating sites, 10 Canadian and the remaining International. The pilot phase will recruit 50 patients from 10 sites (5 Canadian and 5 International). Pilot patients will be included in the final analysis. *While MACE between groups will be tested using the total sample size, we will only be able to detect very large differences at 1 year, as MACE is expected to be approximately 10 - 12% (6,7,17).*

**Table 2a:** Sample Size Estimates for Primary Endpoint (Surgical Arm) – 1-Year Graft Occlusion (two-tailed  $\alpha=0.05$ ,  $\beta=0.20$ )

| Control Event Rate | Relative Risk Reduction |             |                     |             |                     |             |                     |             |                     |             |
|--------------------|-------------------------|-------------|---------------------|-------------|---------------------|-------------|---------------------|-------------|---------------------|-------------|
|                    | 20%                     |             | 25%                 |             | 30%                 |             | 35%                 |             | 40%                 |             |

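### Surgical primary analysis: pre-specify adjustment for target-vessel features fixed before randomization; a cheap gain over a valid unadjusted chi-square test

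*Protocol*

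**What the plan says.** The rationale (Protocol, section 1.A, part II) describes patients now referred for CABG as having small, diffusely diseased, calcified targets. Explaining a ten-year decline, it says: "It is this recent change in the target vessels in contemporary CABG patients, which most likely explains the apparent decrease in 1-year SVG patency".

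Section 5.1 A has one study vein graft per patient, sent to the most important target intended for a vein. The surgeon names that target before surgery. Leg and target are not randomized, but "all site and target vessel characteristics will be recorded for post-hoc multivariable regression analysis".

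Section 8.3 tests the harvest question with a chi-square test by intention to treat. The synopsis agrees: "Comparison of the proportion of patients developing the primary outcome at 1-year using Pearson chi-square test". Modelling of covariates is labelled post hoc. Its list of variables includes "parameters related to the distal coronary artery target such as, size, quality, and factors related to the specific coronary artery grafted", with the severity of the proximal stenosis.

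Section 3.3 stratifies randomization by site and, after the pilot, by control technique (open or endoscopic). Target vessel is not a stratum.

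Section 8.5 A sizes the comparison without any covariate: "A sample size of 615 patients in each group will provide 80% power for a 2-tailed alpha of 0.05", for "20% occlusion rate in the control/ conventional harvesting group, to 14% in the experimental".

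**The concern.** If a shift towards poor targets lowered patency over time, poor targets must occlude more often than good ones. By the protocol's own reasoning the target is therefore prognostic. Because there is one study graft per patient, its target features are single values per patient and simple to adjust for. The plan neither balances them by stratification nor adjusts for them in the primary test.

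Two things are given up. The first is precision: the variation in occlusion that target features explain stays in the error term of a comparison planned at 80% power. The second is protection against a chance excess of poor targets in one harvest group, which would pass directly into the unadjusted risk difference. If the result were borderline, the only adjusted estimate available would be one that the protocol itself calls post hoc.

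**Working it through.** **Inputs from the protocol.** Occlusion 20% v 14%, two-sided alpha 0.05, 80% power, 615 analysed per group (8.5 A). Equal allocation: "At least 1,550 patients will be equally allocated to the four treatment groups" (8.2), so 1:1 for harvest technique. Loss: "We anticipate that 80% of patients will undergo 1-year coronary CT angiography" (8.5 B).

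**Assumed, because the documents do not give it.** One binary target feature ("poor" or "good"), prevalence q = 30% or 50%, odds ratio (OR) for occlusion 1.5, 2, 3 or 5. Marginal rates are held at 20% and 14%.

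**Step 1: reproduce the plan's figure.** With pooled variance under the null and no continuity correction:

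n = [1.96·√(2·0.17·0.83) + 0.8416·√(0.20·0.80 + 0.14·0.86)]² / 0.06² = (1.0412 + 0.4457)² / 0.0036 = 614.1, so 615 per group.

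Power at 615 = Φ[(0.06·√615 − 1.0412) / 0.5295] = Φ(0.844) = 80.1%. After 20% loss, 615 / 0.80 = 768.75, so 769. Both protocol figures reproduce.

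**Step 2: baseline for the comparison.** The unadjusted risk difference has variance (0.16 + 0.1204) / 615, standard error 0.02135, and power Φ(0.06 / 0.02135 − 1.96) = 80.2%. This unpooled form is the fair comparator for step 3.

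**Step 3: adjusted analysis.** For a covariate-standardized risk difference, with r0 and r1 the conventional and no-touch risks within a target class:

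Variance = Σ over classes of w·[2·r0(1−r0) + 2·r1(1−r1) + (r1 − r0 + 0.06)²] / 1,230, where w is the share of the class.

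Example, q = 30%, OR 2. Good targets: 16.5% v 11.3%. Poor targets: 28.3% v 20.3%. The variance is 0.984 of the unadjusted one, the standard error is 0.02118, and power is Φ(0.06 / 0.02118 − 1.96) = 80.9%.

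**Step 4: chance imbalance.** The 95% limit for the difference in poor-target prevalence is 1.96·√[q(1−q)·2/615]: 5.1 points at q = 30%, 5.6 points at q = 50%. Multiplying by the average risk gap between poor and good targets gives the shift in the unadjusted risk difference. At q = 30%, OR 2: 0.0512 × 0.104 = 0.0053, or 0.5 points.

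| OR | Variance ratio | Adjusted power | Gain over 80.2% (points) | Patients per group for the same precision | Shift at 95% imbalance (points) |
|---|---|---|---|---|---|
| 1.5 | 0.994–0.995 | 80.4–80.5% | 0.2 | 612 | 0.3 |
| 2 | 0.984 | 80.9% | 0.6 | 606 | 0.5 |
| 3 | 0.958–0.962 | 81.7–81.9% | 1.5–1.7 | 589–592 | 0.8–0.9 |
| 5 | 0.908–0.928 | 83.1–83.9% | 2.8–3.6 | 559–571 | 1.1–1.3 |

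Ranges run over the two prevalences.

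**Step 5: check by simulation.** With 20,000 trials per setting, stratified Mantel-Haenszel had power of about 0.806, 0.809, 0.820 and 0.833–0.839 at OR 1.5, 2, 3 and 5, against about 0.80 for chi-square. With no treatment effect, both tests rejected in about 5% of trials.

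**The case against.** The strongest case against is that nothing here is wrong. An unadjusted chi-square test is an accepted primary analysis. Its 5% error rate already allows for chance imbalance, and the trial has the power it claims. All of that stands.

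A reader might infer that the protocol names the target vessel as the strongest predictor of graft occlusion. It does not. The sentence explains a fall in patency over a decade. The same section calls graft failure multifactorial and traces its start largely to endothelial injury, and 8.3 lists target parameters unranked among other variables. What survives is the narrower inference that poor targets occlude more often.

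The size rests on assumed odds ratios, and at moderate strength the gain is about one power point. The figures are for a target factor in general, whereas features read before randomization may predict less well than those seen at operation. The primary outcome also counts death from cardiovascular or unknown causes, which target anatomy may not predict equally. Both points could push the gain towards the lower end of the range.

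The post hoc label is also milder than it sounds, because 8.3 names the target variables in advance. But it does not fix which of them enter a model, in what form, or what standing the adjusted estimate has.

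A separate statistical analysis plan could add an adjusted sensitivity analysis. It could not make adjustment primary without departing from a protocol that names the test and calls the models post hoc.

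Finally, the protocol does not say that the target is named before randomization. Surgery may follow by up to 30 days (5.1 B), the surgeon is unblinded to harvest technique (3.1), and Table 1 places surgical details on the day of operation. This does not defeat the point, but it limits which features are safe to adjust for.

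**Conclusion.** The point holds as a cheap improvement. The protocol treats target vessels as important to patency and records them, then leaves them out of both stratification and the primary comparison. Pre-specified adjustment would gain about 0.2 to 4 power points over assumed odds ratios of 1.5 to 5, and roughly 1 to 2 points at 2 to 3. It would also guard against an imbalance that, at its 95% limit, shifts the risk difference by 0.3 to 1.3 points against a planned 6. These figures rest on a single binary factor at 30% or 50% prevalence with 615 analysed per group.

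It would be wrong to conclude that the trial is underpowered or its primary test biased: the stated 80% power reproduces and the error rate is kept.

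**What to change.** In 8.3 and the synopsis, define the surgical primary analysis as a covariate-adjusted comparison: either a logistic model reported as a standardized risk difference, or a stratified Mantel-Haenszel analysis. Adjust for:

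- the intended target's territory and proximal stenosis severity, and vessel size or quality if graded, all read on the preoperative angiogram and entered before allocation is shown;
- the stratification factors (site and control technique).

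State that the intended target remains the covariate even if another vessel is grafted. Keep features graded in theatre by the unblinded surgeon out of the primary model, since allocation could influence them; they can stay in the descriptive models. Retain the Pearson chi-square as the supporting analysis.

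The cost is a paragraph in 8.3, two or three extra fields before randomization, and a requirement to name the target by then, which the protocol does not now make. This assumes that the preoperative angiogram is at hand at that time. The primary estimate also becomes model-based. No extra patients are needed.
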